10.8 Inclusion of Children

Subjects of age 18 or greater will be included in this study. HIV-infected patients of age less than 18 years will be excluded due to the varying effects of puberty on metabolic parameters, inflammatory processes, and endothelial function (the primary outcome measure in the clinical trials proposed in this application).

APPENDIX I: FORMULAS AND DEFINITIONS

1. Cockcroft-Gault Equation [135] for Estimated Creatinine Clearance (CCr)

C-G CCr (mL/min) = [ (140-age) * (weight in kg) * (0.85 if female) / 72] / (SCr in mg/dL)

2. Blood Pressure Measurements: For statistical purposes, the value for the continuous variable of blood pressure will be the mean of the second and third measurements recorded.

3. Waist to Hip Ratio: For statistical purposes, the value for the continuous variable of waist circumference will be the mean of the three midwaist measurements. This value will then be divided by the mean of the three hip circumference measurements.

4. Quantitative Insulin Check Index (QUICKI) [136]

QUICKI = 1 / [ log10(mean glucose) + log10(mean insulin) ],

Where the mean fasting glucose (mg/dL) and insulin (mIU/mL) are those two sets of measurements obtained 10 minutes apart

5. Homeostasis Model Assessment of Insulin Resistance (HOMA-IR) [137]

HOMAIR = mean fasting insulin (µIU/mL) / [22.5 * mean fasting glucose (mmol/L)

Where the mean fasting glucose (mg/dL) and insulin (mIU/mL) are those two sets of measurements obtained 10 minutes apart;

To convert the value for serum glucose in mg/dL to mmol/L, multiply by 0.05551

6. Body Mass Index (BMI)

BMI (kg/m2) = [weight (kg) / height2 (m)]

7. Body Surface Area (BSA)

BSA (m²) = { [height (cm) * weight (kg) ] / 3600}½

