9.3.3 Secondary endpoints analyses

The secondary endpoints are the change in FMD at week 4 and the changes in plasma levels of MCP-1, sVCAM-1, IP-10, fasting lipids, HOMA-IR, CD4 cell count, activated CD8 cell proportions, and HIV-1 RNA level at week 8 from baseline. The secondary analyses will be in exploratory nature and will primarily be used for hypothesis generation. All the secondary outcomes will be analyzed by the same statistical methods as for the primary endpoint. To analyze how the changes in secondary outcomes correlate with changes in FMD, Spearman Rank correlation will be used.

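### The HOMA-IR formula in Appendix I divides by glucose instead of multiplying by it, and the stated insulin units conflict 1000-fold, so a named secondary endpoint would be miscalculated.

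*Combined protocol and SAP*

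**What the plan says.** Section 9.3.3 names HOMA-IR among the secondary endpoints: "fasting lipids, HOMA-IR, CD4 cell count, activated CD8 cell proportions, and HIV-1 RNA level at week 8 from baseline". These endpoints are analysed by the same ANCOVA approach as the primary endpoint, and their changes are correlated with change in FMD by Spearman's method. The section describes the secondary analyses as exploratory.

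Appendix I, item 5, headed "Homeostasis Model Assessment of Insulin Resistance (HOMA-IR", gives the only formula. The numerator is "HOMAIR = mean fasting insulin (µIU/mL"; after the division sign a square bracket opens and contains "22.5 * mean fasting glucose (mmol/L". The bracket is not closed.

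The line beneath reads "Where the mean fasting glucose (mg/dL) and insulin (mIU/mL) are those two sets of measurements obtained 10 minutes apart", and the same wording appears under item 4. For glucose, the appendix bridges the two units: "To convert the value for serum glucose in mg/dL to mmol/L, multiply by 0.05551". It gives no such bridge for insulin.

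Item 4 defines the companion index: "QUICKI = 1 / [ log10(mean glucose) + log10(mean insulin". The sum of two logs is the log of the product, so QUICKI depends on glucose times insulin.

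Section 3.1 lists insulin resistance among the variables to be adjusted for in the final analyses, without naming an index. The closing text of Section 4.2 treats insulin resistance as an outcome worth capturing, because pentoxifylline might prevent it.

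**The concern.** An index of insulin resistance should rise when fasting glucose rises at a given insulin level. As printed, it falls. The appendix therefore contradicts itself: when insulin rises, QUICKI falls and printed HOMA-IR rises, as expected of one index of sensitivity and one of resistance. When glucose rises, both fall. The two indices cannot disagree about insulin and agree about glucose.

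A programmer following the appendix would produce wrong HOMA-IR values for every subject whose glucose is not exactly 1 mmol/L. The size of the error would differ between subjects, and the sign of the change would be wrong for some. That would affect both the treatment comparison and the correlation with FMD. It would also reach the adjusted models if HOMA-IR is the measure of insulin resistance meant in Section 3.1.

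The insulin unit is a separate defect: µIU/mL and mIU/mL differ by a factor of 1000.

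**Working it through.** The document states no HOMA-IR value, so there is no figure of the plan's to reproduce. The check evaluates the printed formula against the product form, with QUICKI as an internal check on direction. The fasting values are illustrative assumptions; the formulas and the conversion factor are from Appendix I. The conversion itself is sound (1/18.016 = 0.05551).

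**Formulas**, with insulin I in µIU/mL and glucose G in mmol/L:
- Printed: I / (22.5 × G)
- Product: I × G / 22.5
- QUICKI: 1 / (log10 glucose in mg/dL + log10 insulin)

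**Size.** At I = 10 and G = 5.0:
- Printed: 10 / (22.5 × 5.0) = 10 / 112.5 = 0.089
- Product: 10 × 5.0 / 22.5 = 2.22

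The ratio of product to printed is G², here 25. At 75, 90 and 125 mg/dL (4.163, 4.996 and 6.939 mmol/L) it is about 17, 25 and 48. Because it varies with each subject's glucose, no constant factor repairs the printed values.

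**Direction.** At I = 15, with G rising from 5.0 to 6.5:
- Product: 75 / 22.5 = 3.33 to 97.5 / 22.5 = 4.33, a rise of 30%
- Printed: 15 / 112.5 = 0.133 to 15 / 146.25 = 0.103, a fall of 23%

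Smaller changes, with QUICKI alongside:

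| Insulin (µIU/mL), glucose (mg/dL) | Printed | Product | QUICKI |
|---|---|---|---|
| 10, 90 | 0.0890 | 2.22 | 0.3385 |
| 10, 110 | 0.0728 | 2.71 | 0.3288 |
| 11, 110 | 0.0801 | 2.99 | 0.3244 |
| 11, 90 | 0.0979 | 2.44 | 0.3338 |

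From the first row to each of the others QUICKI falls (more resistant) and the product form rises. The printed form rises only in the last row, where insulin alone changes; there both HOMA-IR forms rise 10%.

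In general, on the log scale the printed form changes by Δlog I − Δlog G and the product form by Δlog I + Δlog G. These have opposite signs exactly when the log change in glucose is larger in absolute size than that in insulin.

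**How often.** In a simulation with assumed standard deviations of log change of 0.2 to 0.5 for insulin and 0.1 for glucose, and correlation 0 to 0.5, the two forms changed in opposite directions in about 11% to 30% of subjects.

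**Units.** Insulin in mIU/mL (0.010 for 10 µIU/mL) divides HOMA-IR by 1000: the product form becomes 0.00222 instead of 2.22. Applied to everyone, this leaves direction, ANCOVA p-values and Spearman ranks unchanged.

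For QUICKI the effect is not a rescaling. At glucose 90 and 110 mg/dL:
- Insulin 10 µIU/mL: 1 / (1.9542 + 1) = 0.338 and 1 / (2.0414 + 1) = 0.329
- Insulin 0.010 mIU/mL: 1 / (1.9542 − 2) = −21.9 and 1 / (2.0414 − 2) = +24.2

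The index jumps from large negative to large positive as glucose × insulin passes 1.

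**The case against.** - **The line is malformed.** If the bracket were meant to close straight after 22.5, the expression would be the product form, and the error would be typographical. But a bracket around a single number serves no purpose, and item 4 uses the same layout to enclose a whole denominator. The denominator reading is the natural one. At best the line is ambiguous, which an endpoint definition cannot be.
- **The reach is limited.** The secondary analyses are exploratory, HOMA-IR is absent from the numbered objectives in Section 1.0, and the covariates listed in Section 9.3.2 do not include insulin resistance. Section 3.1 does not name HOMA-IR, so the effect on adjusted models is conditional. All of this stands; it limits the damage without making the formula right.
- **The unit conflict does not cause wrong direction.** This also stands for HOMA-IR, where it only changes scale. The m could be a slip for µ, although µ is printed correctly in the formula just above. QUICKI is not a listed endpoint, and its absurd values would probably be noticed.
- **The directional example is chosen to show the effect.** A 30% rise in glucose at fixed insulin is a large change for an 8-week trial that excludes diabetes. The smaller changes in the table reverse too, but where insulin changes dominate the printed form keeps the right direction.
- **An analyst might use the standard formula anyway.** That is possible, but it would mean departing from the written plan.

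**Conclusion.** The concern holds. As printed, the only definition of a named week 8 secondary endpoint puts glucose on the wrong side of the division and contradicts the companion index beside it. Values are too small by a factor of G², about 17 to 48 over glucose of 75 to 125 mg/dL. A subject's change has the wrong sign whenever glucose changes proportionally (on the log scale) more than insulin. The 11% to 30% frequency rests on assumed variability and is only indicative. The insulin unit conflict is real; it is harmless to inference on HOMA-IR if applied consistently, but it destroys QUICKI if taken literally. The primary endpoint analysis in Section 9.3.2 and the sample size are unaffected. The correction must be made before the secondary analyses are programmed.

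**What to change.** In Appendix I:
- Replace the item 5 formula with HOMA-IR = mean fasting insulin (µIU/mL) × mean fasting glucose (mmol/L) / 22.5.
- State insulin as µIU/mL in the unit lines under both items 4 and 5.
- Keep the glucose conversion and make clear that it applies in item 5, while item 4 uses mg/dL.
- Check the analysis program against one worked example: insulin 10 µIU/mL and glucose 90 mg/dL (4.996 mmol/L) should give HOMA-IR 2.22 and QUICKI 0.338.
- In Section 3.1, name the index to be used for the insulin-resistance adjustment.

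This costs a few lines of text and one program check. Visits, assays and data collection do not change, and any values already derived can be recalculated from the stored glucose and insulin results.
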